### Survey and randomization

The enrollment of participants for the baseline survey was based upon a systematic random sampling strategy: (1) selection of wards, (2) household sampling, and (3) individual sampling. These Wards were selected because they are urban/peri-urban and comprise Lusaka, the main city of Zambia. In order to select households, all 40 wards were subdivided into enumeration areas (EAs) based on household density. The centroid point of each EA was generated using ArcGIS version 10.2 software (Esri, Redlands, CA, USA). Centroid points that are within 150 m of the ward boundary were excluded, to avoid enumerators approaching houses that are not in the selected ward. Five EA centroid points and five back-up points will be randomly selected per ward. Enumerator supervisors visited each GPS point and directed enumerators into a Random Walk from each selected EA centroid point, visiting every other house in each direction. A map of Lusaka wards and an example of the sampling strategy are detailed in Fig. 2. Interviewers visit households in the mornings and afternoons, and on weekends, when participants are likely to be home. When the enumerator visits a selected household, he/she records a roster of individuals living in that house. The roster assigns each individual a number, then one individual is randomly selected for participation. If that participant is not eligible, the next randomly selected individual from the roster will be approached. If no one is eligible, then the house will be labeled “no one eligible.” If the participant is home but busy, the interviewer will schedule an appointment for a later time. If no one is home, the interviewer will approach one additional time. If no one is home at the second visit, then a GPS coordinate is recorded and the household labeled “no one available.” If the individual at the household refuses to participate, then the household will be labeled “refused.”

A structured questionnaire was administered to each eligible and consented individual who met the inclusion criteria. Survey interviewers were either male or female and work for Innovations for Poverty Action (IPA) Zambia. Each interview lasted about one hour and took place in the home but away from other household members, in private. The questionnaire collects socio-demographic information, information regarding condom use, sexual behavior, knowledge and beliefs specifically regarding condoms, contraceptive options, and communication with sexual partners. A small reimbursement amount was provided to participants who completed the survey. The study enrolled both men and women.

After the baseline survey was completed in January 2016, all 40 wards were randomized to receive the control (WC plus mass media) or intervention (WC plus mass media plus IPC), and were allocated by an IPA statistician using a Stata program. Ward level population density based on the 2010 census data, ward level poverty, and average distance to the nearest health facility were used to stratify the randomization. Additional balance checks were conducted to ensure randomization was successful. Each ward has been mapped including the IPC sites, and all visited houses enumerated and given an ID. Since randomization, the IPC intervention has been implemented in intervention wards only. Only the IPA statistician and the implementing partner (the SFH) know the allocation of wards. The endline survey is planned for March 2017, and will follow the same protocol as outlined above for the baseline survey. The endline survey will have additional questions regarding exposure to the mass media and IPC intervention, including pictures to prompt recall. Households will be randomly selected for both surveys; the same households will not be approached.

The Consolidated Standards of Reporting Trials (CONSORT) randomization and survey structure are described in Fig. 3.

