### Data management and analysis plan

The data are collected into an Android phone using SurveyCTO software; the data obtained are cleaned and exported into Stata for analysis. A high frequency check is run every two to three days to highlight any errors in data collection. Twenty percent of all participants (eligible or ineligible) are being randomly selected for back checking. The back check includes confirmation of ineligibility or administration of a 5- to 10-min version of the original survey to compare responses. All data are encrypted using Boxcryptor and stored on the SurveyCTO cloud and Box. A de-identified version of the data and statistical code will be shared on Dataverse at the completion of the study.

We will report the trial according to the CONSORT standards for reporting RCTs. This is a behavioral intervention unlikely to produce adverse effects, so analysis will be undertaken immediately once the endline survey has been completed. Baseline survey data will be analyzed to measure differences between the groups and between the wards at baseline. Randomization can be checked at this point. The main analysis will take place after endline data have been collected, to measure the impact of the introduction of the WC and the IPC intervention on condom use, controlling for any potential confounders or explanatory factors detected from the baseline analysis.

To assess the impact of the introduction of the new and premium WC on the Zambian condom market, the evaluation team will use the baseline survey as a quasi-control arm. While there are limitations with this approach, it will allow for measurement of changes in condom use, brand switching, user preferences, and uptake of the new product. The main limitation is that the study cannot determine attribution; however, given the challenges to create a better counterfactual, the evaluating and implementing teams agreed that this is the best approach in view of programmatic constraints.

The baseline survey will occurred at a time when there was no WC product available, no mass media, and no IPC. The study outcomes are self-reported condom (male or female) use ever, during the past 6 months, and at last sexual intercourse. The study will measure these indicators at baseline (no WC available) and endline (WC available). By analyzing changes in these indicators, the study will show changes in overall condom use as well as uptake of the WC in areas with only mass media versus mass media and IPC.

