For the RCT component of the study, we will analyze the impact of the IPC intervention on our outcomes of interest (male condom use, WC use, willingness to use the WC), comparing intervention to control wards. Analyses will be conducted in Stata v12 (StataCorp, College Station, TX, USA). Results will be adjusted for any ward level clustering if it is identified. Multivariate regression analyses will be carried out to determine the impact of the IPC intervention on condom use (male condom and WC), controlling for demographic characteristics of participants.

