#### Statistical methods

For the primary and secondary outcomes we will estimate odds ratios with 95% confidence intervals. We will calculate the rates of self-reported contraception use per ward and willingness to use the WC. Descriptive analyses will be conducted, and several regression models will be run to determine the impact of IPC on each outcome variable of interest. All regression models will control for baseline characteristics of relevance to the outcome (either as potential confounders or as explanatory factors). Backward elimination methods will be used to remove non-statistically significant factors that do not improve the fit of the model and do not confound other associations observed. Multilevel models may be implemented to control for individual and ward level correlation, as individuals are nested within wards.

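### The plan does not secure the stratification variables or ward baseline prevalence in the IPC models, and its backward elimination can remove them, at a cost in precision

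*Protocol article*

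**What the plan says.** Survey and randomization, on how the 40 wards were allocated: "Ward level population density based on the 2010 census data, ward level poverty, and average distance to the nearest health facility were used to stratify". That section also makes the two surveys separate samples: "Households will be randomly selected for both surveys; the same households will not be approached".

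The covariates are described in three places, in three ways:

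- Data management and analysis plan, on the main analysis: "controlling for any potential confounders or explanatory factors detected from the baseline analysis". The preceding step is described as: "Baseline survey data will be analyzed to measure differences between the groups and between the wards at baseline".
- The same section, in the paragraph on the RCT component: "controlling for demographic characteristics of participants".
- Statistical methods: "All regression models will control for baseline characteristics of relevance to the outcome (either as potential confounders or as explanatory factors"). Then comes the selection rule: "Backward elimination methods will be used to remove non-statistically significant factors that do not improve the fit of the model". The rest of that sentence adds a further condition: a factor is removed only if it also does not confound other associations.

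The stratification variables are not mentioned in any of these places, and neither is the ward's baseline prevalence of the outcome. No term is exempt from the elimination rule.

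**The concern.** Variables used to stratify the allocation would normally stay in the analysis model whatever their p-value, because they were chosen as likely predictors of outcome and the design was built around them. Here a stated selection rule decides whether they stay. Its two safeguards protect them poorly. Stratification balances these variables across arms, so they should show little confounding of the IPC effect. Ward-level terms are tested on only 40 wards, so a useful predictor can easily miss significance.

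The baseline survey raises the same issue. Different households are sampled each time, so the baseline outcome can enter the IPC comparison only as a ward-level value. That value may be a strong predictor of the ward's endline prevalence, and it has already been collected. If it is left out or eliminated, removable between-ward variance stays in the estimate.

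**Working it through.** **The article's own figure.** Table 2 gives 526 per arm. Then 526 × 2 = 1052 for clustering, and 1052 × 1.10 = 1157 for refusals. This chain reproduces. The 526 itself comes from SD 0.15, a 3-point difference and 90% power: 2 × (1.960 + 1.282)² × 0.15² / 0.03² ≈ 526. At the stated 80% power the result is 393. That discrepancy, and the use of SD 0.15 for a binary outcome, are separate matters. The check below uses the binomial variance at 53%.

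**Inputs from the article.** Control prevalence 53%; 1157 per arm; 20 wards per arm, so m = 1157/20 = 57.85 (58 in the text); design effect 2; 80% power; 5% significance level, taken as two-sided.

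**Assumption, not in the article.** c is the correlation of true ward prevalence between the two surveys. It is shown at 0.6, 0.8 and 1.0.

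**Step 1, implied ICC.** 2 = 1 + (m − 1) × ICC, so ICC = 1/56.85 = 0.0176.

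**Step 2, unadjusted precision.** SE = √(2 × 0.53 × 0.47 × 2 / 1157) = 2.93 points. Detectable difference = (1.960 + 0.842) × 2.93 = 8.2 points. With t quantiles on 38 degrees of freedom it is about 8.4.

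**Step 3, reliability of an observed ward mean.** R = m × ICC / design effect = 57.85 × 0.0176 / 2 = 0.509.

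**Step 4, adjusting for ward baseline prevalence.** The observed ward means correlate at r = R × c, and the variance is multiplied by 1 − r².

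| c | r | Variance reduction | Detectable difference |
|---|---|---|---|
| 0.6 | 0.305 | 9% | 8.2 × √0.907 = 7.8 |
| 0.8 | 0.407 | 17% | 8.2 × √0.834 = 7.5 |
| 1.0 | 0.509 | 26% | 8.2 × √0.741 = 7.1 |

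**Step 5, sensitivity to ICC.** With c = 0.8, the variance reduction is about 9% at an assumed ICC of 0.01 and about 36% at 0.05.

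**Step 6, stratifiers alone.** If they explain a share q of the between-ward variance (assumed), the reduction is R × q: about 5%, 15% or 25% for q = 0.1, 0.3 or 0.5. This overlaps with the gain in Step 4, so the two should not be added.

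**Step 7, why the form of the baseline term matters.** The Data management and analysis plan also speaks of changes from baseline to endline by arm, without giving a model. At c = 0.8, relative to an endline-only comparison (1.00), a simple change score has variance 2(1 − r) = 2 × (1 − 0.407) = 1.19, and adjustment for ward baseline has 1 − 0.407² = 0.83. The text permits all three.

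**Limits.** The formulas treat wards as equal in size, work on the risk-difference scale and ignore the degrees of freedom spent. The article will report odds ratios, for which adjustment does not follow the same variance formula. The figures apply to any condom use only. The Woman's Condom (WC) was not available at baseline, so its baseline use is zero in every ward and cannot serve as a covariate.

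**The case against.** A reader might infer from the RCT paragraph that the IPC analysis adjusts for demographics alone and ignores the stratifiers and the baseline survey. The article does not support that. Statistical methods applies to all regression models and allows any relevant baseline characteristic. The main analysis is to control for factors found in a baseline analysis that looks between wards. The primary IPC objectives refer to controlling for differences between the arms, and change by arm is mentioned. The terms are permitted but not fixed.

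A reader might also infer biased estimates or confidence intervals that are too narrow. That does not follow either. Leaving out predictive stratifiers usually makes the standard error too large, provided ward clustering is in the model. The conditional wording on clustering, "Results will be adjusted for any ward level clustering if it is identified", is a separate question.

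Three further objections have weight. A ward variable that explains much of the outcome would tend to improve fit and survive elimination, so the terms most at risk are those that add least; this limits the loss, but significance on 40 wards is still an unreliable guide. A full covariate list is commonly left to an analysis plan, so not naming one would be no finding; the point here is that the article states a selection rule that exposes design variables to deletion, and describes the covariates in three different ways. Finally, the size of the gain rests on quantities that the article does not give. That stands, and is why ranges are shown.

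**Conclusion.** The point holds as one of unsecured terms. The randomisation was stratified on three ward variables and baseline condom use was measured in all 40 wards, but the IPC models are not committed to keep either, and the elimination rule can remove both.

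The consequence is lost precision. For any condom use, the recoverable variance is about 9% to 26% under the article's design effect of 2 and an assumed between-survey correlation of 0.6 to 1.0. The upper end supposes that true ward prevalences are perfectly correlated between surveys over more than a year in which a new product is launched, so it is a ceiling. In detectable difference the gain is about 0.4 to 1.1 points from 8.2. For WC use and willingness to use it, any gain is unknown. This is a worthwhile correction that should be made before the endline data are analysed.

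**What to change.** In Statistical methods, state that every IPC model keeps the following terms, exempt from backward elimination:

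- the randomisation stratification variables (population density, poverty, distance to a health facility), in a parsimonious form suited to 40 wards;
- where the outcome was measurable at baseline, the ward's baseline prevalence of that outcome, entered as a covariate and not as a change score;
- for WC use, the ward's baseline any-condom use as a proxy;
- for willingness to use the WC, the ward's baseline interest in using a female condom, which Table 1 lists among the baseline outcomes, as a proxy.

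Then reconcile the covariate statements in the Data management and analysis plan and in Statistical methods so that one description applies.

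No new data are needed. The cost is in ward-level degrees of freedom, of which there are 40 − 2 = 38. Three linear stratifiers plus one baseline term use 3 + 1 = 4. Fully crossed categories cost more: even two levels each give 2 × 2 × 2 = 8 strata, so 7 + 1 = 8, and finer cuts take more. The article does not say how the variables were categorised, so the form should be chosen and stated before the endline data are seen.

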**Fig. 3 Fig3:**
[figure not shown]
CONSORT flow diagram of study design

### Primary and secondary outcomes

The primary and secondary outcomes listed below correspond to the primary and secondary objectives.

The primary outcomes are:Increase in the *prevalence (percentage) of WC* (self-reported) use among men and women aged 18–24 years evereverlast 6 months,most recent sexual intercourse.

2.Increase in the *prevalence (percentage) of any condom* (self-reported) use among men and women aged 18–24 yearseverin the past 6 months at most recent sexual intercourse.

3.Increase in the *willingness to use* the WC in the future among men and women aged 18–24 years.

The secondary outcomes are:4.Self-reported increase in knowledge, improved attitudes, and practices of both male and female condoms after attending IPC intervention5.Self-reported increase in acceptability (community awareness) of FCs6.Self-reported improvement in communication with sexual partner(s) regarding use of male and/or female condoms for STI prevention and/or family planning7.Self-reported condom brand preference before and after rollout of the WC.

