**Methods/design:**

A baseline survey of 2314 randomly selected 18- to 24-year-old sexually active men and women has been conducted. The WC and mass media will be introduced throughout 40 urban wards in and surrounding Lusaka, Zambia. The baseline survey will serve as a quasi-control arm to determine the impact of introducing the WC with mass media. Half of the wards will be randomly allocated to additionally receive the IPC intervention. A single-blind randomized controlled trial will determine the impact of the IPC intervention on knowledge, uptake, and use of the WC. After one year, another 2314 individuals will be randomly selected to participate in the endline survey.

We hypothesize that (1) the distribution and media campaign of the WC will increase overall condom use in selected urban wards, and specifically use of the WC; (2) the IPC intervention will significantly impact knowledge, acceptability, and use of the WC.

The primary outcome measures are use of the WC, use of any condom, and willingness to use the WC. Secondary outcomes include measures of knowledge, acceptability, and choice of contraception.

Odds ratios will be estimated to measure the effect of the intervention on the outcomes with 95% confidence intervals. All analyses will be based on the intention-to-treat principle.

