
### Sample size

To calculate the sample size needed in each trial arm, we considered prevalence of any condom use (percentage) as our outcome of interest. The contraceptive prevalence rate (CPR) for any modern contraceptive method in urban Zambia (for 15- to 49-year-old married women) is currently about 53% [4]. However, our study includes both married and unmarried women. A report from 2009 by the Zambian Statistics Office reported urban condom use to be 54% in Zambia [7]. We used 53% to calculate our sample size, and aim to detect a minimum increase of 5% use with 80% power at the 95% significance level. Because the trial is clustered at the ward level (with many individuals living within a ward), the sample size needs to be increased to account for intraclass correlation (ICC) within wards. However, no information was found from previous studies on the likely between- or within-cluster correlations in FC use in previous cluster-randomized trials. When the ICC cannot be estimated, common practice is to double the sample size to account for clustering.

Using Stata (StataCorp, College Station, TX, USA), we calculated the sample size required to detect a 4%, 5%, and 7% increase in any use from a 53% baseline use and an estimated standard deviation (SD) of 0.15, doubling the sample size to account for the unknown ICC. Lastly, we added 10% to increase the sample size to account for potential refusals. We will use a sample size of 1157 individuals per arm (a total of 2314 individuals in both arms). This yields a total of 58 individuals to be interviewed per ward, in a total of 40 wards (see Table 2).

**Table 2 Tab2:** Sample size required to detect a 2, 3, and 4 percentage point increase in condom use (4%, 5%, and 7% increase)

Hypothesized standard deviation of condom use	Hypothesized increase in proportion of condom use between groups	Sample size required in each group (ratio 1:1)	Adjusted for effect of clustering (design effect = 2)	10% refusal rate (estimated)
0.15	7%	296	592	651
0.15	5%	526	1052	1157
0.15	4%	1183	2366	2603

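### Up to seven unranked measures are primary for the IPC comparison, the sized one has no recall window, and ever use of any condom counts use before IPC began

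*Protocol article*

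**What the plan says.** All places are in the protocol article.

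- *Primary and secondary outcomes* lists three numbered primary outcomes: "Increase in the *prevalence (percentage) of WC* (self-reported) use among men and women aged" 18–24 years, "Increase in the *prevalence (percentage) of any condom* (self-reported) use among men and women aged" 18–24 years, and "Increase in the *willingness to use* the WC in the future among men and women aged" 18–24 years. The first two carry three recall windows each: ever, 6 months and most recent intercourse. In the copy reviewed the windows of the first outcome are run together, so the total is given here as up to seven.
- *Data management and analysis plan* repeats the windows: "The study outcomes are self-reported condom (male or female) use ever, during the past 6 months, and at last sexual intercourse". For the randomized comparison, the same section names male condom use, WC use and willingness, not any condom use.
- The *Abstract* names three outcomes and no windows: "The primary outcome measures are use of the WC, use of any condom, and willingness to use the WC". Its second hypothesis, on IPC, names knowledge, acceptability and use of the WC.
- *Statistical methods*: "For the primary and secondary outcomes we will estimate odds ratios with 95% confidence intervals".
- *Sample size*: "we considered prevalence of any condom use (percentage) as our outcome of interest", with no window.
- *Table 1* gives condom use (male at baseline, WC at endline) over 6 months and last intercourse only. It omits ever use.

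**The concern.** Naming the primary outcome is a design decision, and the protocol has made it: several overlapping measures share the label and none leads. A correction for multiplicity could sit in an unseen analysis plan, but an analysis plan would inherit this list and the disagreements between sections. As it stands, the outcome and window that answer the IPC question could be settled after the endline data are seen.

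One of the measures is also poorly suited to the question. Ever use of any condom is cumulative and cannot be reversed. Respondents are sexually active 18- to 24-year-olds, the *Discussion* describes male condoms as widely available and cheap, and the intervention lasts about one year. A respondent who used a condom before IPC counts as a success in either arm, whatever IPC does. Ever WC use does not share this problem, because no WC was available at baseline.

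**Working it through.** **1. The plan's own figure.** Inputs from *Sample size*: a rise of 3 percentage points, SD 0.15, design effect 2, 10% added for refusals. With n = 2(z₁₋α/₂ + z₁₋β)² × SD²/δ² and two-sided α = 0.05:

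- 90% power: 2 × (1.960 + 1.282)² × 0.0225/0.0009 gives 526 per arm, which matches Table 2. Then 526 × 2 = 1052, and 1052 × 1.10 = 1157.
- 80% power, as the text states: 393 per arm. This mismatch is a separate matter.

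The calculation covers one outcome at α = 0.05, with no window named.

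**2. Count.** 3 (WC use) + 3 (any condom use) + 1 (willingness) = 7.

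**3. False-positive chance if any one of seven counts.** Each test is two-sided at 0.05. Correlated cases were simulated with 400,000 multivariate-normal draws. All correlations are assumptions.

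| Correlation among windows of one outcome | All other pairs | Chance of at least one false positive |
|---|---|---|
| 0 | 0 | 1 − 0.95⁷ = 30.2% |
| 0.3 | 0.3 | 27.2% |
| 0.5 | 0.2 | 26.6% |
| 0.7 | 0.3 | 23.2% |
| 0.8 | 0.5 | 19.6% |
| 0.9 | 0.5 | 17.6% |
| 0.9 | 0.9 | 11.4% |

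The first row cannot occur. Eligibility requires sex in the last 6 months, so use at last sex lies within 6-month use, which lies within ever use. WC use also lies within any condom use. The row is only an upper bound.

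**4. Ever use of any condom.** If a share p had already used a condom, IPC can act only on 1 − p. A 3-point gain then needs 0.03/(1 − p) of never-users to convert. The documents give no value of p for ever use.

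| Assumed p | Never-users who must convert |
|---|---|
| 53% (planning value for condom use, window unstated) | 0.03/0.47 = 6.4% |
| 70% | 0.03/0.30 = 10% |
| 80% | 0.03/0.20 = 15% |
| 90% | 0.03/0.10 = 30% |

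The 3-point target was set for condom use without a window. Applying it to ever use is a choice made here for illustration.

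**5. Is 6 months a workable window?** Roll-out was set for February 2016. The endline is given as January 2017 (*Trial status*) or March 2017 (*Setting and participants*). Six months back is July or September 2016, after roll-out in both cases.

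**6. Price of error control.** On the plan's SD, 526 per arm and 3 points, power is 90% at α = 0.05. It is 80% at Holm's strictest step for three tests (0.05/3 = 0.0167) and 71% with Bonferroni over seven (0.05/7 = 0.0071).

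**7. Should any condom use be tested first, as a gate?** As a yes/no outcome at 53% versus 56%, with an effective 1052/2 = 526 per arm, the standard error is √[(0.53 × 0.47 + 0.56 × 0.44)/526] = 0.031. Then 0.03/0.031 ≈ 0.98, and power is Φ(0.98 − 1.96) ≈ 16%. A gate on this outcome would usually block the test of WC use.

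**The case against.** The strongest reply is that this is a condensed article. Testing order and multiplicity rules are commonly left to an analysis plan, and a 95% interval is a statement about estimation. The objectives treat WC use, any condom use and willingness separately, and whether distinct objectives need joint error control is debated. No section says that one significant result out of seven would count as success, and if all seven had to succeed, type I error would not rise and power would fall instead. This stands as a limit: the inflation is conditional on the any-one reading. It does not remove the point, because the list of primary measures, the windowless sizing and the disagreements between sections are all in the article.

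Three stronger readings are tempting and not supported:

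- A reader might infer a 30% false-positive risk. That requires independence, which the nested windows rule out.
- A reader might infer that ever use of any condom is largely fixed before IPC. The direction is certain, but no ever-use rate is given. At 53% only about 6% of never-users would need to convert, and some younger respondents may have become sexually active during the intervention year.
- A reader might infer that a flat ever-use result dilutes the any-condom answer. No section pools the windows, so the other two estimates are unaffected. Ever use also has a legitimate place in the baseline-to-endline market comparison.

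**Conclusion.** The point holds as a weakness in how the primary outcomes are fixed. Up to seven measures are primary for the IPC comparison with no lead, the outcome used for sizing has no window, and Table 1 and the analysis section do not match the outcome list. If any single significant result may be presented as a primary success, the false-positive chance is about 11% to 27% for assumed pairwise correlations of 0.9 down to 0.3, roughly two to five times the nominal 5%.

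Ever use of any condom is a poor primary measure for IPC because it counts use that IPC cannot alter. The extent depends on an ever-use rate that the documents do not give. This should be settled before the endline data are analysed.

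**What to change.** Before endline analysis:

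- Keep WC use, any condom use and willingness as the three primary outcomes of the IPC comparison.
- Use the past 6 months as the single window for both use outcomes. It lies wholly after roll-out and matches the 6-month residence and sexual-activity criteria.
- Test the three by Holm at an overall two-sided 5%, comparing the ordered p-values with 0.0167, 0.025 and 0.05. Do not make any condom use a gate.
- Move last-sex use and ever WC use to secondary.
- Keep ever use of any condom as descriptive, including in the baseline-to-endline market comparison.
- Align Table 1, *Sample size* and *Data management and analysis plan* with this list, and say whether the randomized comparison concerns male condom use or any condom use.

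The cost is mainly wording, with fewer headline endpoints and somewhat stricter thresholds. On the plan's own inputs, power falls from 90% to 80% at Holm's strictest step. Those inputs use an SD of 0.15. For a yes/no outcome near 53%, power is already about 16% at α = 0.05 and about 8% at 0.0167. That is a sizing problem this change neither causes nor cures.
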